### 1.6. Objectives and Hypotheses

The primary objective is to evaluate the attitudes of Romanian adults recruited online—acceptability, trust, risk perception, and responsibility attribution—toward four progressive scenarios of AI implementation in facial reconstructive surgery. The secondary objectives are (i) to analyze the moderating effect of AI familiarity on acceptability across autonomy levels; (ii) to investigate how responsibility attribution (surgeon, hospital, AI developer, unavoidable medical uncertainty) varies across scenarios; (iii) to explore the moral–legal distinction in responsibility attribution; (iv) to identify the preferred model of AI implementation in facial reconstructive surgery; and (v) to quantify the influence of presentation sequence on all primary outcomes and to estimate the autonomy effect adjusted for serial position.

Four hypotheses will be tested. H1. Acceptability and trust decrease significantly as the level of AI autonomy in the surgical decision increases. H2. Perceived risk increases as human control over the decision process decreases. H3. Responsibility attribution shifts progressively from the surgeon toward the AI developer as algorithmic autonomy increases. H4. Prior familiarity with AI moderates the relationship between implementation scenario and acceptability, such that participants familiar with AI show a smaller decline in acceptability for high-autonomy scenarios; H4 is treated as partially exploratory, given the power constraints described in Section 2.5. H1–H3 fix the expected direction but not the functional form: each is tested by an omnibus effect of autonomy level followed by the full set of orthogonal polynomial contrasts, so that threshold-like or otherwise non-monotonic patterns are detected rather than forced into a linear trajectory (Section 2.9.1). A design-validation hypothesis is tested alongside them, namely that responses do not depend on the sequence in which the scenarios were presented; it is evaluated as the scenario × sequence interaction, and a non-null result is treated as evidence of order dependence to be reported and adjusted for, not as a substantive finding about autonomy.

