
#### 2.9.2. Secondary and Exploratory Analyses

(i) Moderation (H4): the scenario × AI familiarity (B1, centered) interaction, via repeated-measures ANCOVA or a linear mixed model with random intercepts per participant, the recommended framework for vignette data [62]; presentation sequence is retained as a between-subjects factor here, as in every repeated-measures model in this protocol. (ii) Person-level multiple regression: mean acceptability across scenarios predicted by AI familiarity, general AI attitudes, and demographics (reporting *B*, *SE*, β, 95% CI, R^2^, VIF). (iii) Responsibility migration (H3): a 4 × 4 mixed ANOVA (scenario × actor, RES1–RES4, both within-subjects; presentation sequence between-subjects) with Greenhouse–Geisser correction; the scenario × actor interaction is the direct test of H3. Because H3 is confirmatory, it receives the same order controls as H1 and H2: the sequence terms are inspected first, and the migration estimate is repeated in a linear mixed model containing an additive serial-position term. (iv) Responsibility concentration: a normalized Herfindahl–Hirschman index computed per scenario from the relative weights of the three responsible actors (surgeon, hospital, AI developer; RES4—unavoidable medical uncertainty—is not a responsible actor and is analyzed separately), compared across scenarios by mixed repeated-measures ANOVA with sequence as a between-subjects factor; low values index diffusion of responsibility across actors, operationalizing the “problem of many hands” described in the responsibility literature [44,45]. (v) RES5 (moral duty) and RES6 (outcome-independent accountability): mixed repeated-measures ANOVAs across scenarios with sequence as a between-subjects factor, Holm-corrected within the family. (vi) Global preference (P1): a goodness-of-fit chi-square with standardized residuals over six analysis categories on 5 degrees of freedom. The six categories are the four scenarios, “I would prefer AI not to be involved in any way,” and a combined “no clear preference” category; the last pools the item’s two undecided options (“I have no preference” and “I cannot decide”), which are combined a priori because neither expresses a preference between scenarios and each is expected to be sparse. Consistency between stated preference and each participant’s maximum-acceptability scenario is reported descriptively. (vii) Exploratory: P4a and P4b (the surgeon’s permanent legal and, separately, moral responsibility) analyzed descriptively, compared with each other by a dependent-samples test on the within-person difference, and correlated with RES5/RES6; free-text concerns (P2) summarized by brief thematic analysis. (viii) Sensitivity analyses: primary analyses repeated (a) excluding participants with a single attention-check failure (who are retained under the primary rule) and (b) excluding participants with any comprehension failure, to demonstrate that conclusions do not depend on the cleaning criteria [69]. (ix) Order effects: descriptive profiles by sequence, the scenario × sequence interaction with its effect size and 95% confidence interval, and sequence-specific manipulation-check profiles. (x) Response-pattern typology (exploratory): where the random-slope test of Section 2.9.1 indicates heterogeneity, individual acceptability trajectories across autonomy levels are classified by latent-class growth analysis, with class enumeration by BIC and entropy and a minimum class size of 5% fixed in advance, and class membership described against AI familiarity, healthcare-system trust, and demographics; no inferential claim is attached to this analysis. (xi) Healthcare-system trust (B6) enters the person-level regression of (ii) as a covariate and is examined as an exploratory moderator of the autonomy effect, alongside healthcare contact frequency (B5) and prior surgical experience (B4, B4a). (xii) Subgroup analyses, all of which are secondary or exploratory, are governed by a minimum-cell rule fixed in advance: inferential tests within a subgroup are reported only where that subgroup contains at least 50 valid participants, the size at which a within-subject difference in *dz* = 0.40 is detectable at power 0.80; subgroups of 30–49 are reported descriptively with 95% confidence intervals and labeled as underpowered; subgroups below 30 are pooled into a residual category or not reported. A difference between subgroups is never inferred from a significant effect in one and a non-significant effect in another; only the formal interaction term, with its own confidence interval, supports such a claim. The set of moderators is fixed a priori, in the pre-registration, to seven: AI familiarity (B1), healthcare-system trust (B6), healthcare contact frequency (B5), prior surgical experience (B4/B4a), education (D3), age (D2), and field of activity (D4). Results are reported for all seven irrespective of significance, and no further moderator is added after the data are seen. (xiii) Missing data: because all closed items are mandatory, missingness in the dependent variables is structurally impossible within a submitted questionnaire. Two other forms of missingness remain. The first is unit-level, from questionnaires abandoned before submission. The platform is configured not to store partial submissions, so responses from abandoned questionnaires are neither retained nor analyzed (Section 2.10 and Appendix A.1). Attrition is therefore characterized from the platform’s page-level counters—how many participants reached each page—rather than from partial response data, and is reported as drop-out by serial position in the participant-flow diagram. Analyses are accordingly restricted to complete cases, that is, participants with all four scenario blocks, and no imputation is performed: with no partial records retained, there are no incomplete cases to impute. The second is item-level, on the background and demographic items that offer a “prefer not to answer” option or, in the case of B4 and B4a, are not displayed where the explicit health-data consent is declined; these are treated as a distinct category descriptively and as missing in inferential models, with a sensitivity analysis retaining the category in the person-level regression. Because complete-case analysis is not neutral when attrition is differential, drop-out is compared across the four presentation sequences, and any imbalance is reported and carried into the interpretation of the order analyses. All tests are two-tailed at α = 0.05, with exact *p*-values, effect sizes, and 95% confidence intervals reported for all tests, including non-significant ones. On closed 1–7 scales, no distribution-based outlier removal is applied.

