## Figures and Tables

**Figure 1 healthcare-14-03030-f001:**
[figure not shown]
Achieved power of the primary repeated-measures ANOVA (four within-subject levels, α = 0.05) as a function of the number of valid responses, for small (*f* = 0.10, at ρ = 0.50 and ρ = 0.30) and medium (*f* = 0.25) effects. Dotted reference lines mark power = 0.80 and the two pre-specified thresholds (*N* = 140, minimum analyzable; *N* = 300, recruitment target). Curves are computed analytically from the noncentral *F* distribution. Entering presentation sequence as a between-subjects factor consumes three degrees of freedom from the error term and leaves these curves unchanged to within rounding.

**Table 1 healthcare-14-03030-t001:** The four experimental scenarios. The labels A–D denote autonomy level, not position in the sequence; scenarios are administered in one of four counterbalanced sequences (see Section 2.1).

Scenario	Label	Role of the AI System	Role of the Surgeon
A	Imaging assistance	Analyzes the CT scan and highlights anatomical structures (e.g., bone density, tissue layers)	Independently interprets the AI output and makes all decisions on the surgical plan
B	Decision support	Proposes three possible surgical plans, each with different advantages and disadvantages	Reviews all options, selects the most suitable plan, and may adjust it
C	Outcome simulation	Generates 3D simulations of postoperative facial appearance for each surgical option	Reviews the simulations, discusses them with the patient, and decides the final plan
D	Autonomous planning	Generates a complete, optimized surgical plan	Reviews the plan before surgery; modifications to the AI proposal are rare

**Table 2 healthcare-14-03030-t002:** Minimum detectable effects (power = 0.80, α = 0.05).

Test	Parameters	Minimum Detectable Effect
RM-ANOVA, 4 within-subject levels	*N* = 24, ρ = 0.50	*f* = 0.25 (medium)
RM-ANOVA, 4 within-subject levels	*N* = 140, ρ = 0.50	*f* = 0.10 (small)
RM-ANOVA, 4 within-subject levels	*N* = 300, ρ = 0.50	*f* = 0.07
Dependent pairwise comparison	*N* = 300, α = 0.05	*dz* = 0.16
Dependent pairwise comparison	*N* = 300, α = 0.05/6	*dz* = 0.20
Scenario × familiarity interaction (*df* = 3)	*N* = 300, α = 0.05	*f*^2^ = 0.037
Goodness-of-fit chi-square, preference (*df* = 5)	*N* = 300, α = 0.05	*w* = 0.21
Autonomy main effect, sequence as between-subjects factor (*df* = 3)	*N* = 300, ρ = 0.50	*f* = 0.07

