Scenario × sequence interaction—order test (*df* = 9)	*N* = 300, ρ = 0.50	*f* = 0.08
Scenario × sequence interaction—order test (*df* = 9)	*N* = 300, ρ = 0.30	*f* = 0.10
Pilot order bound, ascending vs. descending arm (*df* = 3)	*N* = 50, ρ = 0.50	*f* = 0.17
Dependent comparison within a demographic subgroup	*n* = 50, α = 0.05	*dz* = 0.40

Abbreviations: RM-ANOVA, repeated-measures analysis of variance; *N*, number of valid participants; *n*, number of participants per pilot arm or subgroup; ρ, correlation between repeated measurements; α, significance threshold; *df*, degrees of freedom; f and *f*^2^, Cohen’s effect-size indices for *F* tests; *dz*, Cohen’s effect size for dependent-samples comparisons; *w*, effect size for the goodness-of-fit chi-square test.

**Table 3 healthcare-14-03030-t003:** Projected recruitment funnel.

Stage	Assumed Pass Rate	Estimated Number
Link accesses	—	≈545
Begin questionnaire (consent given)	85% of accesses	≈463
Eligible after screening (items S1, S2)	96% of starters	≈445
Completed (submitted) questionnaires	75% of eligible	≈334
Valid after quality exclusions (ATT, CC, invariant, duplicates)	90% of submitted	≈300

Abbreviations: S1 and S2, the two screening items of the instrument (Appendix A.1); ATT1 and ATT2, attention checks; CC_A–CC_D, comprehension checks.

**Table 4 healthcare-14-03030-t004:** Measurement structure of the instrument.

Construct/Variable	Items	Scale	Role in Analysis
Acceptability	ACC1–ACC3 (mean), per scenario (×4)	Likert 1–7	Primary DV (H1), within-subjects
Trust	TRU1–TRU3 (mean), per scenario (×4)	Likert 1–7	Primary DV (H1), within-subjects
Perceived risk	RSK1 (reversed), RSK2, RSK3 (mean), per scenario (×4)	Likert 1–7	Primary DV (H2), within-subjects
Responsibility attribution	RES1–RES4, per scenario (×4)	Likert 1–7	Secondary DV (H3), within-subjects
Responsibility principles	RES5, RES6, per scenario (×4)	Likert 1–7	Secondary DV
Global preference	P1	7 response options (6 analysis categories)	Secondary DV
General acceptability	P3	Likert 1–7	Secondary DV
AI familiarity	B1	Likert 1–7	Moderator (H4)/covariate
General AI attitudes	G1–G4 (G2, G4 reversed)	Likert 1–7	Covariates
Experience and demographics	B2–B5, D1–D7	Mixed	Covariates/sample description
Manipulation check (perceived AI control)	MAN1, per scenario (×4)	Likert 1–7	Design validation
Scenario difficulty	DIF1, per scenario (×4)	Likert 1–7	Control covariate (fatigue)
Data quality	ATT1, ATT2, CC_A–CC_D	Categorical	Exclusion criteria

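### The six-category chi-square on stated preference (P1) mixes preference among the four scenarios with the no-AI and undecided shares, so a significant result need not show any preference among scenarios

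*Protocol article*

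**What the plan says.** Secondary objective (iv) in Section 1.6 is "to identify the preferred model of AI implementation in facial reconstructive surgery". The inferential analysis given for stated preference is Section 2.9.2(vi): "a goodness-of-fit chi-square with standardized residuals over six analysis categories on 5 degrees of freedom". The cells are listed there: "The six categories are the four scenarios, “I would prefer AI not to be involved in any way,” and a combined “no clear preference” category". Two response options are merged to form that final cell, "which are combined a priori because neither expresses a preference between scenarios and each is expected to be sparse". Table 4 correspondingly lists seven response options and six analysis categories.

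Section 2.5 and Table 2 (row "Goodness-of-fit chi-square, preference") give a minimum detectable w of 0.21 on 5 df at N = 300, and Section 2.5 names this test among the person-level analyses that set the target of 300. Table 5 lists the output as the chi-square, its df, p, w and standardized residuals, with a descriptive check against each participant's maximum-acceptability scenario. The article does not write out the null shares, and it lists no inferential test of P1 restricted to the four scenarios.

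**The concern.** Objective (iv) asks which implementation model people prefer. A goodness-of-fit test answers that only if its null hypothesis says that the models are equally preferred. With six cells and 5 df, the natural null says something broader: that each scenario, the no-AI answer and the undecided pool all attract one sixth of respondents. Two of those six shares are not comparisons between scenarios. The undecided pool is described that way by the plan itself, and the no-AI answer rejects all four scenarios alike.

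If either share differs from one sixth, the null is false even when the four scenarios are exactly tied. The p-value and w would then be reported under a global-preference label while saying nothing about which model is preferred. The article treats a parallel case differently: in Section 2.9.2(iv), RES4 is left out of the concentration index because it is not a responsible actor, and it is analysed separately.

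**Working it through.** **Inputs from the protocol article.** Six categories, 5 df (2.9.2(vi)); N = 300, power 0.80, α = 0.05, detectable w = 0.21 (2.5, Table 2).

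**Assumptions not in the article.** Null share 1/6 per cell; undecided share q and no-AI share r, shown as ranges.

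**Step 1: the plan's own figure.** Power is the probability that a noncentral chi-square on 5 df, with noncentrality λ = N·w², exceeds the critical value 11.07. Power 0.80 needs λ = 12.83, so w = √(12.83/300) = 0.207, which rounds to the stated 0.21.

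**Step 2: vary the undecided share, with the other five options tied.** Each of the five has share (1 − q)/5. Then

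w = √{6·[5·((1 − q)/5 − 1/6)² + (q − 1/6)²]}.

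For q = 0.05, the other shares are 0.19 and w = √{6·[5·(0.0233)² + (0.1167)²]} = √0.098 = 0.313, so λ = 300 × 0.098 = 29.4 and the rejection probability is 0.995.

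| Undecided share q | w | Rejection probability, N = 300 |
|---|---|---|
| 2% | 0.39 | about 1.00 |
| 5% | 0.31 | 0.995 |
| 8% | 0.23 | 0.895 |
| 10% | 0.18 | 0.66 |
| 12% | 0.125 | 0.34 |
| 14% | 0.07 | 0.13 |
| 16.7% | 0 | 0.05 |

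Multinomial simulation (40,000 draws) gives above 0.999 at 5%, 0.95 at 8%, 0.70 at 10%, 0.34 at 12% and 0.13 at 14%. By the formula, rejection reaches 80% once q is about 9% or less. At the lowest analytic floor, N = 140, the formula gives 0.83 at 5% and 0.33 at 10%.

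**Step 3: vary the no-AI share, with the scenarios tied.** Take q = 1/6 and r = 0.25. Each scenario then has (1 − 1/6 − 0.25)/4 = 0.1458, and w = √{6·[4·(0.0208)² + (0.0833)²]} = 0.228. So λ = 15.6 and rejection is 0.88. With q = r = 0.10 it is 0.98.

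**Step 4: what the residuals would show.** At q = 0.05 the expected count per cell is 50. The undecided residual is (15 − 50)/√50 = −4.95, and each tied option has (57 − 50)/√50 = +0.99.

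**Step 5: two replacements.**
- *Drop only the undecided pool (five cells, 4 df, null 1/5).* With 285 respondents, the scenarios tied and no-AI at 10%, w² = 5·[4·(0.225 − 0.2)² + (0.1 − 0.2)²] = 0.0625, λ = 17.8 and rejection is 0.94. No-AI at 30% gives the same. The problem remains through the no-AI cell.
- *Four scenarios only (3 df, null 1/4).* With the scenarios tied, simulated rejection is 0.050 to 0.052 at n = 216 to 240. Power 0.80 needs λ = 10.90, so the detectable w is √(10.90/240) = 0.213 and √(10.90/216) = 0.225. If only half of the 300 chose a scenario (n = 150), it would be √(10.90/150) = 0.27.

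**The case against.** The strongest reply is that the plan already includes standardized residuals. Step 4 supports this: at a 5% undecided share, the undecided cell stands out at about −5 while the tied options sit near +1. A careful reader would usually see the cause. That stands, and it limits the practical harm. It does not close the gap, because the residuals are measured against the same null of sixths and give no test of equality among the scenarios, and p and w are reported regardless.

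Second, P1 is secondary, and the confirmatory set is H1–H3 with the manipulation and order checks. Differences in acceptability between scenarios are tested separately in Section 2.9.1. This too is correct, and it keeps the point modest. Those contrasts concern ratings, however, and not the stated choice.

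Third, the null shares are inferred and may be set in an analysis plan that is not shown. The obvious alternative, one seventh per response option and hence 2/7 for the pool, does not help. With the five other options tied at N = 300, rejection is above 0.999 at q = 10% and 0.96 at q = 16.7%.

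A reader might also infer that the pool is known to be sparse, and so that the test is bound to reject. The article does not support that. It expects each of the two undecided options to be sparse, pooling makes the cell larger, and no share is given for the pool. Near one sixth, rejection is nominal.

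**Conclusion.** The point holds in a limited form. The article fixes a test whose null, on the natural reading, combines equality among scenarios with specific shares for two cells that do not compare scenarios. A significant 5-df result or a w above 0.21 therefore does not by itself serve objective (iv). Under equal sixths at N = 300, with the four scenarios and no-AI tied, false attribution to preference is near certain when the undecided share is 5% or less, about two in three at 10%, and small from 14% up to one sixth. A no-AI share away from one sixth has the same effect independently.

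This rests on the inferred null and on shares that the article does not give. It does not follow that the test must reject, that the residuals are useless, or that the stated detectable effect is wrong: w = 0.21 reproduces. What changes is the meaning of a significant result, and a better test costs little.

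**What to change.** In Section 2.9.2(vi), make the inferential test for objective (iv) an equal-share chi-square over the four scenarios among participants who choose one (3 df, null 1/4 each), with its standardized residuals. Report the no-AI and undecided shares separately, each with a 95% confidence interval, over all valid participants. If the six-category test is kept, state its null shares and label it as descriptive of the whole response distribution.

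Amend the P1 rows of Tables 2 and 5 and the corresponding sentence in Section 2.5 to 3 df. Give the detectable w for a stated number choosing a scenario: about 0.21 at n = 240 and 0.22 at n = 216.

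The cost is a few sentences and a smaller analysed n. Sensitivity is almost unchanged unless many respondents choose no-AI or are undecided. Data collection has not started, so the change can go into the pre-registration.

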
### 2.3. Participants: Eligibility Criteria

Inclusion criteria: age ≥ 18 years; current residence in Romania; ability to read and complete an online questionnaire in Romanian; and informed consent expressed by ticking the consent checkbox on the first page of the instrument. Exclusion criteria applied at screening: age < 18 years, residence outside Romania, or refusal of consent. Exclusion criteria were applied at data cleaning, following current recommendations for careless-responding control [68,69]: failure of both embedded attention checks; incorrect response to the comprehension check—after re-presentation of the scenario (second attempt)—for at least two of the four scenarios; invariant response patterns (the same response selected for every Likert-type item in the questionnaire); and duplicate records (identical response patterns across all variables, submitted consecutively).

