
### 2.7. Data Quality Procedures

Four mechanisms protect data quality, consistent with current best-practice recommendations for careless-responding prevention and detection [68,69] and with multi-layered approaches to online-survey integrity [72]. First, two attention checks are embedded in the questionnaire: ATT1, an instructed-response item placed after the general attitudes section (participants are asked to select a specific scale point regardless of their opinion), and ATT2, a content check after the scenario blocks asking which type of surgery the scenarios described. Exclusion applies only when both checks are failed. Second, each vignette is followed by a single multiple-choice comprehension check targeting the scenario’s defining feature (who made the final decision, or what the AI’s role was). A first incorrect response triggers branching that re-presents the full scenario, after which the check is repeated; a second incorrect response flags that scenario as failed (CC_*x*_FAIL = 1), and participants failing at least two of the four scenarios are excluded. Third, invariant response patterns (identical responses to all Likert items, including across scenarios) and duplicate records are screened during data cleaning. Fourth, all closed questions are mandatory on the survey platform, structurally preventing item-level missingness in the dependent variables; “prefer not to answer” options exist only for selected background and demographic items (B4, B4a, B5, B6, D1, D6, D7) and are coded as a distinct category descriptively and as missing in inferential models; participants who decline the separate explicit consent for the two health-related items (Section 2.10) are not presented with items B4 and B4a, and those records are coded in the same way. The platform does not record completion time, so data quality relies on the checks above rather than on a temporal filter; this is declared as a limitation. Finally, each participant’s sequence allocation (SEQ) is made at the point of entry to the scenario blocks and written to the submitted record, and the platform maintains its page counters separately for each sequence. Drop-out can therefore be attributed to a sequence and a serial position even where no submission is stored. Balance across the four sequences is monitored during accrual and reported in the participant-flow diagram, and section-wise drop-out is tabulated by serial position as well as by scenario, so that fatigue can be distinguished from a reaction to a particular scenario. The comprehension checks remain valid under counterbalancing because each is bound to the scenario it immediately follows, and ATT2 concerns content common to all four scenarios.

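### Both cleaning sensitivity analyses only tighten the exclusion rules, so they cannot show that conclusions are independent of those rules

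*Protocol article*

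**What the plan says.** Sections 2.3 and 2.7 of the protocol article set four exclusions at data cleaning.

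- Attention: "Exclusion applies only when both checks are failed".
- Comprehension: "incorrect response to the comprehension check—after re-presentation of the scenario (second attempt)—for at least two of the four scenarios".
- Invariance: the same answer to every Likert-type item.
- Duplicates: identical records submitted one after another.

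Section 2.5 and Table 3 assume that 90% of submitted questionnaires survive these rules, taking about 334 submissions to about 300 valid ones.

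Section 2.9.2 (viii) then repeats the primary analyses in two ways: (a) "excluding participants with a single attention-check failure (who are retained under the primary rule") and (b) "excluding participants with any comprehension failure". The stated purpose is "to demonstrate that conclusions do not depend on the cleaning criteria".

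On sequence, Section 2.9.2 (xiii) says that "drop-out is compared across the four presentation sequences, and any imbalance is reported". Section 2.12 promises a flow diagram with exclusion counts for each rule and analysed counts for each sequence.

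**The concern.** A sensitivity analysis of a cleaning rule should show what the result would have been had the rule been looser or absent. Here both variants start from the cleaned sample and remove more people. A reader told that the conclusions do not depend on the cleaning criteria would take this to cover the records that were thrown out, and no planned analysis looks at those.

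Two of the rules are linked to the effect under study. An invariant responder shows no difference between scenarios at all, so removing such records can only enlarge the absolute mean contrast. The comprehension checks are built on what distinguishes the scenarios (Section 2.2), so people who fail them repeatedly may plausibly show a flatter gradient. At stake is a stated robustness property of H1–H3 that the listed analyses cannot deliver. No primary test or sample size is affected.

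**Working it through.** **1. The plan's funnel (Section 2.5, Table 3).** Inputs: 545 link accesses; pass rates 0.85, 0.96, 0.75 and 0.90.

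- 545 × 0.85 = 463.3
- × 0.96 = 444.7
- × 0.75 = 333.5 (stated as about 334)
- × 0.90 = 300.2 (stated as about 300)

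The plan's figures reproduce. The quality rules remove 334 − 300 = 34 records, and 34/334 = 10.2% of submissions.

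**2. The analysed sets.** Let P be the primary sample after all four exclusions.

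- Set (a) is P without those who failed exactly one attention check.
- Set (b) is P without those who had any comprehension failure. Those with two or more second-attempt failures are already gone, since "participants failing at least two of the four scenarios are excluded".

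Both sets lie inside P. Of the 34 removed records, (a) restores 0 and (b) restores 0. Neither set touches the invariance rule.

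**3. What an invariant record contributes.** Suppose every item is answered k in every scenario.

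- Acceptability and trust composites both equal k in each scenario.
- The risk composite, with its one reversed item, is [(8 − k) + k + k]/3 = (8 + k)/3 in each scenario.
- RES1–RES4 all equal k in each scenario.

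Every between-scenario difference is therefore exactly zero, and so is the record's contribution to the scenario × actor interaction that tests H3. This follows from the definition and needs no assumption about behaviour.

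**4. Illustrative size.** Assume the 300 retained records have a standardised paired difference d = 0.20 (the plan's smallest effect of interest, Section 2.9.1) with SD 1, and the 34 restored records have mean difference 0. With w = 300/334 = 0.898:

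- Mean contrast: 0.898 × 0.20 = 0.180, which is 0.90 of the retained-sample value.
- Variance: w + (1 − w)s² + w(1 − w)d², where s is the SD of the restored records' differences.
- s = 1: dz = 0.180/√1.004 = 0.179; t = 0.179 × √334 = 3.28.
- s = 0 (as for invariant responders): dz = 0.180/√0.902 = 0.189; t = 0.189 × √334 = 3.46.
- Retained sample alone: t = 0.20 × √300 = 3.46.

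Under the zero-gradient assumption, dz falls from 0.20 to between 0.18 and 0.19. If the restored records instead showed an equal and opposite difference, the same formula gives dz of 0.16 to 0.17. The documents offer no basis for preferring either case.

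**The case against.** **The two planned analyses are not empty.** If people with comprehension failures have a flatter gradient, dropping those with a single failure should raise the estimate, and the plan reports effect sizes with intervals. This stands. A reader might infer that agreement between (a), (b) and the primary result is to be expected even when cleaning drives the effect. The documents do not support that: a stable estimate under (b) is some evidence against the mechanism, though incomplete.

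**The comprehension rule is a defensible choice.** It requires a second failure, after the scenario has been shown again, in at least two scenarios. The checks ask about the decision-maker only in A and B; in C they ask about the system's role, and in D about the origin of the plan followed. This stands as a defence of the primary rule. It also means that a reader should not infer that the rule simply removes people who missed who decides, or that the reported gradient is known to be inflated. For comprehension failers that direction is plausible but not shown.

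**The dilution is small.** At dz = 0.20 every t value under the zero-gradient assumption exceeds about 2.65, the Bonferroni critical value for six tests. This stands too. A larger loss can be computed by taking the pilot's 70% first-attempt threshold as the main-study rate. The chance of failing at least two of four scenarios, 1 − (1 − q)⁴ − 4q(1 − q)³ under independence, is then 11% if half pass on the second attempt (q = 0.15) and 4% if 70% do (q = 0.09). But 70% is an acceptance floor, and the documents give no second-attempt rate.

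**Sequence balance is largely covered.** A reader might infer that unequal exclusions would pass unseen and undermine sequence as a randomised factor. Section 2.12 already gives both margins, Section 2.7 monitors balance, and the autonomy contrast is within-person. Only the joint table of rule by sequence is absent.

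**A separate analysis plan may add more.** A sensitivity set omitted from an article would be no finding. This point rests on something else: the article lists the analyses, says what they demonstrate, and the listed ones cannot demonstrate it.

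**Conclusion.** The concern holds as an overclaim with an easy remedy. Analyses (a) and (b) can support robustness to stricter cleaning and nothing wider. None of the roughly 34 of 334 removed records is restored by any planned analysis, and the invariance rule is left unvaried although the effect of its removals on the mean contrast has a known direction.

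The logical gap depends on no assumption. Its size does. The 10% is a planning rate, not an observed one. The 0.90 ratio assumes no gradient in any removed record, and it is the upper end under that assumption because the 34 include duplicates, which should stay out. The primary exclusion rule is not shown to be wrong, and the primary result is not shown to be biased.

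**What to change.** Keep the primary rule and add to Section 2.9.2 (viii): *(c) all submitted, eligible, non-duplicate questionnaires, with no attention, comprehension or invariance exclusion*, for H1–H3 and the adjacent-pair contrasts. State robustness to the cleaning criteria only if (a), (b) and (c) agree. Otherwise, limit the statement to robustness against stricter cleaning.

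Optionally, cross-tabulate quality exclusions by rule and sequence next to the planned drop-out comparison.

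The cost is one further run of existing models. Section 2.11 already keeps the attention and comprehension flags and the allocated sequence in the dataset, and pre-registration is still to come (Section 2.12). The downside is that (c) readmits careless responders and may give a diluted secondary estimate, so it should be read as a bound on the influence of cleaning and not as a replacement for the primary result.
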